##### Mechanism of Action (Effect Mediators) and Modifiers

###### Resources

We will ask participants to report resources they have access to at baseline and follow-up. We will ask the same FT4W-specific questions as in the feasibility study [10] and use the following constructs from the Social Determinants of Health Collection of the PhenX Toolkit, a set of standardized measurement protocols used in health equity research [33,34]: health insurance coverage and food insecurity. We will also measure access to childcare [35].

###### Social Cohesion and Support

We will measure participants’ perception of social cohesion in their neighborhood with 4 previously validated, standardized questions from the 2018 National Health Interview Survey using a 5-point Likert scale [36]. Questions ask about participants’ perceptions of help availability, neighbors’ accountability, trust in neighbors, and close-knit neighbors in their neighborhood. We will also administer the Medical Outcomes Study Social Support Survey, which asks participants to rate how often different types of social support are available to them when needed, such as someone to confide in or someone to help with chores if sick [37]. Finally, we will also administer the Sense of Community Index-2 at follow-up only (specifically asking about the FT4W group), which captures group belonging by examining the intersection of interpersonal and community influence in the sociocultural environment, byproducts of human relationships that are difficult to capture by measuring social networks and peer support. Previous evidence demonstrates that the Sense of Community Index-2 strongly predicts behaviors such as participation [38,39].

###### Intersecting Social Stratifiers

Intersectionality considers the interaction of different social stratifiers (eg, race or ethnicity, indigeneity, gender, class, sexuality, geography, age, disability or ability, migration status, and religion) and underlying multilevel power structures [33]. We will administer questionnaires at baseline and follow-up and use the responses for individual quantitative data. At baseline, we will assess individual social stratifiers using measures from the Social Determinants of Health Collection of the PhenX Toolkit [40]: ethnicity and race, biological sex assigned at birth, gender identity, sexual orientation, educational attainment (individual), health insurance coverage, and current employment status. We will also ask about migration status, language preference, number and age of children, as well as the degree to which their neighborhood supports physical activity through the Physical Activity Neighborhood Environment Survey [41]. While previous health disparity research considers forms of social stratification in isolation or in an additive manner [40], intersectionality is multilevel and calls for analysis that is more than just a sum of its parts. Thus, quantitative methods are limited. We will use qualitative methods to explore how intersecting factors at the individual, community, and institutional levels modify effectiveness and implementation. We will specifically explore how SEP, race, and ethnicity intersect when it comes to the FT4W experience.

#### Data Collection

##### Quantitative Data Collection

###### Baseline Assessment

Participants will receive individualized links via text message to complete the online baseline questionnaire, which assesses participant demographics, physical activity, health status and well-being, social cohesion, access to childcare, and individual- and community-level social determinants of health.

Study staff will send a preprogrammed Axivity AX3 watch mailed directly to the participant following completion of the baseline survey (week 0). Participants will be asked to wear the Axivity watch on their nondominant wrist for 24 hours per day for 8 full days and to complete the accompanying sleep diary every day, either on paper or via text message, based on their preference. Instructions on how to use the watch and complete the diary will be included in the parcel via written materials and a brief video. Following 8 days of wear, the participant will post the accelerometer (free of charge in prestamped envelopes) back to the project coordinator, who will check the data for completeness. If the data do not meet our quality control checks and there are at least 2 weeks remaining before the first scheduled class, then we will mail another accelerometer to the participant. A previous study conducted with the same population found nonadherence to waist accelerometers to be 35% [42]. Data from the National Health and Nutrition Examination Survey also show that adherence to wrist accelerometers is higher (70%-80%) than waist accelerometers (40%-70%); therefore, we expect adherence to wrist accelerometers to be 75% in our study [43]. To increase adherence, we will send automated text reminders to confirm receipt of the accelerometer, to complete the accompanying sleep diary every day, either on paper or via text message, and to return the accelerometer.

###### Follow-Up Assessment

At week 10, study staff will again mail Axivity AX3 watches to participants and links to complete the online follow-up questionnaire, following the same procedure as baseline. We will consider them lost to follow-up if we do not receive a response by week 16.

##### Qualitative Data Collection

###### Overview

Ethnographic methods will be used to examine how intersecting forms of social inequality shape women’s experiences of physical activity in the context of their broader lives (studying the experiences of research participants) and to understand how real-world conditions shape the intervention implementation (studying the workings of the research team and the impacts of the changing social context on study implementation). The field ethnographer will be bilingual and of the same approximate age as the research participants and will be supervised by the team’s senior ethnographer.

###### Ethnographic Research With Study Participants and Intervention Activities

The field ethnographer will conduct participant observation, which will entail participating in at least 6 fitness classes (2 in each arm) and 4 peer support activities in each study wave throughout the trial. Through participant observation, the ethnographer will use a structured note-taking form to record observations about group dynamics, social environment, expressions of cultural norms, expressions of frustration at challenges of getting to exercise class, and other individual comments or social interactions relevant to understanding challenges women with children face in engaging in physical activity, including related to childcare, as well as how the intervention assets (childcare and social support) do or do not facilitate their participation in Shape Up NYC classes. For each instance of participant observation, the ethnographer will also record the time of day, weather, and time of year to assess temporal impacts on participation. The ethnographer will take both brief field notes on their phone during childcare drop-off, before and after classes, and during social support activities, expanding these into more complete notes after leaving the study site. Notes will describe the physical conditions, the effect of mother-child dyads at drop-off and pickup, how participants engage with each other and the instructor, and what is said or expressed through body language about the classes and activities.

Group message data for arm C will serve as an additional source of qualitative data. Through content analysis, researchers will assess topics of discussion, jokes, expressions of friendliness, the development of connections between research participants, the sharing of information, and other content types to shed light on what social support consists of and how it might affect participation in physical activity. We will also quantify the number of interactions in the chat per wave.

###### Ethnographic Case-Control Research

Through comparing participants who engage in high and low rates of physical activity, ethnographic case-control research may shed light on otherwise unmeasured factors that affect the outcome as well as social, cultural, and structural barriers to physical activity. Purposive sampling for the ethnographic case-control study will use data from accelerometers to identify women with low and high levels of each outcome and then recruit individuals who meet the criteria for diversity specified in Table 1. We will select pairs of cases and controls within arms and match on race and ethnicity. We will select pairs from all arms within the same wave.

**Table 1 table1:** Ethnographic case-control sample.

Race and ethnicity			High physical activity, n		Low physical activity, n
**Black**					
	Non-Hispanic	4		4	
	Hispanic	4		4	
**White**					
	Hispanic	4		4	

After the week 12 follow-up, the field ethnographer will conduct semistructured interviews with those recruited for this purposive sample to gain further insight into participants’ views and experiences with FT4W and specifically to understand differences in individual characteristics, social context, or access to resources, which might lead the intervention to be impactful for some and not for others. Interviews will be audio-recorded and transcribed. We expect to complete ~48 interviews or until we reach data saturation as recommended for this type of study [44].

###### Development and Fidelity of Intervention Protocol

Ethnographic research conducted by the senior ethnographer, with a focus on the development of the intervention itself, will generate an understanding of how factors internal to the team (team process, particularities, and power dynamics) and factors external to the team (the political and social context) shape the development and implementation of the intervention protocol, including fidelity to the proposed intervention.

The study itself is an object of inquiry. To do this, the senior ethnographer will participate in all study team and CAB meetings and use a checklist to track development, fidelity, and changes to the protocol based on real-world demands. In addition, the senior ethnographer will conduct key informant interviews with study team members and community partners to learn about community organizations’ experience of the intervention implementation, including policy factors and other potential challenges to sustainability. Finally, over the duration of the project, the senior and field ethnographers will compile information about how the broader social context (eg, budget cuts due to the migrant crisis in New York City) shapes the implementation of the project.

#### Data Monitoring

Data monitoring by the study team will occur at least on a biannual basis (ie, every 6 months). Participant enrollment (including compliance with protocol enrollment criteria), data completeness, and the status of all enrolled participants will be reviewed by the PI and supported by the study team.

This study will be stopped prior to its completion if (1) the intervention is associated with adverse effects that call into question the safety of the intervention, (2) difficulty in study recruitment or retention will significantly impact the ability to evaluate the study end points, (3) any new information becomes available during the trial that necessitates stopping the trial, or (4) other situations occur that might warrant stopping the trial.

#### Analyses

##### Quantitative Analysis

The primary analyses will be on the intention-to-treat sample: all randomized participants according to the assigned treatment. Missing data on outcome variables will be dealt with by using multiple imputation or inverse probability weighting of cases with complete data, where we will calculate weights based on the probability of a participant being a completer versus a dropout. We will conduct a sensitivity analysis to provide a range of plausible effect estimates that could arise due to nonignorable missing data.

For aims 1 and 2, we will use linear mixed-effects models (LMMs) to assess the main intervention effects on physical activity outcomes and other secondary outcomes. The outcome measure of interest will be the dependent variable; the treatment arm (categorical variable with 3 categories) will be the predictor. Cluster-specific random intercept will account for intraclass correlation. We will further adjust the model for baseline covariates that are not balanced across treatment groups (if any). Comparison of treatment arms can be tested by forming contrasts of regression coefficients in the models.

We will conduct mediation analysis to test whether environmental resources and social cohesion, described under working mechanisms, mediate the intervention effects. For each mediation analysis, we will conduct 2 LMM analyses. The first model will use the outcome measure as a dependent variable and treatment arm and mediator as predictors. The second model will use the mediator as a dependent variable and treatment arm as the predictor. Both models will include a cluster-specific random intercept to account for intraclass correlation. Causal mediation effects will be tested using the R package *mediation*. For aim 3, moderator analysis will examine whether intervention effects differ across social stratification parameters (stratifier) at the individual and community levels. We will conduct a similar LMM analysis as in the main effect analysis, with the exception that each stratifier and its interaction with the treatment arm will be included in the LMM. The moderator effect will be examined by testing the stratifier by treatment interaction effect coefficients.

While 21 clusters are on par with the average cluster size in cluster RCTs, we still need to correct for the small sample since type I error can be up to ~7% for studies with 20-40 clusters [45]. For our continuous outcomes, residual (restricted) maximum likelihood will be used [46]. We will also adjust the test statistic to a 2-tailed *t* test with 2K–2 degrees of freedom if cluster structures are balanced [47]. If cluster sizes vary, alternative small sample corrections will be used. As a sensitivity analysis, cluster-level analysis will also be conducted. We will perform a 2-tailed *t* test on the cluster-level means of physical activity.

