### Outcomes

#### Primary Outcome: Physical Activity

The primary outcome will be total minutes of time spent in MVPA per week. We will objectively assess weekly MVPA, total physical activity, sedentary time, and sleep using a blinded research-grade wrist-worn accelerometer (Axivity AX3) in all groups.

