**Assessments**																	
	Baseline accelerometer (AX3) measurement		✓														
	Baseline questionnaire		✓														
	Attendance data collection			✓	✓	✓	✓	✓	✓	✓	✓	✓	✓	✓	✓		
	Follow-up accelerometer (AX3) measurement												✓	✓	✓		
	Follow-up questionnaire												✓	✓	✓		
	Interviews (for purposively selected participants only)															✓	

^a^W: wave.

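### Baseline accelerometer MVPA enters the primary model only if it happens to look unbalanced between arms; it should be a prespecified covariate

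*Protocol article*

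**What the plan says.** The primary outcome is fixed under Primary Outcome: "The primary outcome will be total minutes of time spent in MVPA per week", measured by wrist accelerometer. The model is set in Quantitative Analysis. "The outcome measure of interest will be the dependent variable", "the treatment arm (categorical variable with 3 categories) will be the predictor", and "Cluster-specific random intercept will account for intraclass correlation". The dependent variable is therefore the outcome itself; no change score or repeated-measures model is described. The only provision for covariates is "We will further adjust the model for baseline covariates that are not balanced across treatment groups (if any".

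Baseline accelerometry is part of the design. Under Baseline Assessment: "Study staff will send a preprogrammed Axivity AX3 watch mailed directly to the participant following completion of the baseline survey (week 0". Table 2 lists "Baseline accelerometer (AX3) measurement" at enrollment for each wave. At follow-up the watches are mailed again, "following the same procedure as baseline".

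**The concern.** A covariate improves a randomized comparison in so far as it predicts the outcome. Whether it differs between arms in the observed sample is a poor guide to that. A rule based on imbalance can bring in covariates with no prognostic value and leave out a strongly prognostic one that happens to be balanced. The baseline value of the outcome, taken with the same device and procedure, is the natural first candidate for adjustment, and here its entry is left to chance.

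Two things are at stake. The first is precision, in a trial with 7 sites per arm and a stated detectable effect of 0.68 SD. The second is that the form of the primary model is unknown until the baseline data have been inspected, and with no criterion stated, two analysts could defend different primary models on the same data.

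**Working it through.** **Inputs from the Sample Size section:** k = 7 sites per arm, m = 15 analyzable participants per site, ICC = 0.15, 80% power, 5% significance (taken as two-sided) for B versus A, and Bonferroni over two comparisons (2.5% each) for arm C. **Assumed:** the baseline to follow-up correlation r of MVPA, which the document does not give; range 0.3 to 0.7.

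**1. The plan's own figure.** Design effect DE = 1 + (15 − 1) × 0.15 = 3.1. Detectable effect = (z for alpha + z for power) × √(2 × DE / (k × m)).
- B versus A: (1.960 + 0.842) × √(6.2/105) = 2.802 × 0.243 = 0.68, as stated.
- Arm C comparisons: (2.241 + 0.842) × 0.243 = 0.75, as stated.

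Both match with normal quantiles and without the stated coefficient of variation of 0.5 in cluster size. That is a separate matter. The proportional gains below do not depend on the starting value.

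**2. Always adjusting, r equal within and between clusters.** The detectable effect is multiplied by √(1 − r²).

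| r | factor | B versus A | arm C |
|---|---|---|---|
| 0.3 | 0.954 | 0.65 | 0.72 |
| 0.5 | 0.866 | 0.59 | 0.65 |
| 0.7 | 0.714 | 0.49 | 0.54 |

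**3. Always adjusting, baseline explains only within-cluster variance.** A cluster mean has variance 0.15 + 0.85/15 = 0.2067, of which 0.15/0.2067 = 73% lies between clusters and 27% within. The factor becomes √(1 − 0.274 × r²).

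| r within | factor | B versus A |
|---|---|---|
| 0.3 | 0.988 | 0.67 |
| 0.5 | 0.965 | 0.66 |
| 0.7 | 0.930 | 0.63 |

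Across steps 2 and 3 the reduction runs from about 1% to 29%.

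**4. What the imbalance rule does.** Simulation of 40,000 trials per setting: 7 versus 7 balanced clusters, cluster means with the variance in step 3 and baseline to follow-up correlation r. The unadjusted t test has 12 df and the adjusted analysis 11 df. Power is at a true d of 0.68. It starts at 0.73 rather than 0.80 because t rather than normal quantiles are used. The plan states no trigger, so two were tried.

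| Analysis | Type I error, r = 0.3 / 0.5 / 0.7 | Power, r = 0.3 / 0.5 / 0.7 |
|---|---|---|
| Never adjust | 0.051 / 0.051 / 0.049 | 0.73 / 0.73 / 0.73 |
| Always adjust | 0.051 / 0.051 / 0.050 | 0.73 / 0.80 / 0.92 |
| Adjust if baseline differs at p<0.05 | 0.049 / 0.045 / 0.037 | 0.72 / 0.73 / 0.74 |
| Adjust if baseline differs by more than 0.2 SD | 0.047 / 0.040 / 0.030 | 0.72 / 0.75 / 0.82 |
| Report whichever p value is smaller | 0.067 / 0.075 / 0.082 | not a valid test |

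With the significance trigger, almost all the available power gain is lost at r = 0.5 and 0.7. In the spread of the estimate at r = 0.7, the SD is 0.243 unadjusted, 0.230 under the rule and 0.182 always adjusted, so about a fifth of the gain is kept (0.013/0.061). The 0.2 SD trigger, which fires in about 41% of trials, recovers most of the reduction in spread (SD 0.190). It recovers only about a third (r = 0.5) to a half (r = 0.7) of the power gain. At r = 0.3 always adjusting brings no power gain in this cluster-level analysis, because the lost degree of freedom offsets it.

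**The case against.** **The covariate list belongs in the analysis plan, which is not shown.** True of a list, and its absence is no complaint here. But the article states a selection rule, and an analysis plan that fixed baseline MVPA in advance would depart from it.

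**Baseline MVPA is not excluded.** A reader might infer that the trial discards it. The text does not say so: it can enter if judged unbalanced, and the planned imputation or weighting could also use it. What stands is that its place in the analysis model is conditional on the data.

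**The rule is written down and does not itself inflate type I error.** Correct. A fixed p<0.05 trigger is slightly conservative. The inflation in the last row of the table needs a free choice between results, which the article does not prescribe. It only leaves room for it by naming no criterion.

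**The gain may be small.** This stands. About 73% of the cluster-mean variance is between clusters, so the gain depends mainly on the between-cluster correlation, for which no figure is given. The expected 25% accelerometer nonadherence would reduce it further. A reader might take a reduction of 13% to 29% as given, or apply it to a detectable effect of 0.81. The first needs r of 0.5 to 0.7 at both levels. The second arises only by combining a cluster-size-inflated design effect (3.66) with t quantiles on 12 df; the article states 0.68.

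**Selection imbalance.** Because sites are randomized before participants are recruited, a reader might infer that baseline imbalance through selection is likely. The article has partial safeguards: recruitment under blinding, allocation withheld from the principal investigator and coordinators, a masked study purpose, and stratification by location and season. Community partners are unblinded and circulate flyers, so some risk remains, but the document does not show it to be likely.

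**Conclusion.** The point holds as a badly fixed rule, not as an invalid analysis. The unadjusted model is valid. The defect is that the most obvious prognostic covariate, already collected, enters the primary model only through an undefined imbalance check. With a significance trigger, that check gives up most of the precision that adjustment would bring.

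The size is uncertain. The B versus A detectable effect of 0.68 would fall by between about 1% (r = 0.3, within-cluster variance only) and 29% (r = 0.7 at both levels). This rests on an assumed r, on the Sample Size inputs, and on baseline records being available. The case for fixing the covariate in advance does not depend on r: it removes the dependence of the primary model on the data and the scope for a choice that could take type I error to about 0.08.

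**What to change.** Delete the imbalance rule. Prespecify the primary linear mixed model as follow-up MVPA on arm plus baseline MVPA, with the cluster random intercept. Put the baseline value of each secondary outcome in its own model where one is collected; attendance, for example, has none.

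State how participants without a valid baseline record stay in the intention-to-treat analysis, for example by a named method of baseline imputation. The present missing-data text covers outcome variables only. Move any other covariate adjustment to sensitivity analysis.

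The cost is analysis wording plus the handling of missing baseline wear; no new data are needed. Recruitment was still open at submission (471 enrolled), so the change can be made and dated before any outcome is examined by arm.

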**Methods:**

This study comprises a 3-arm parallel cluster randomized controlled trial (RCT) with low-resourced mothers living in New York City. We will randomize fitness class sites (clusters) into arm A (contact control), receipt of free weekly fitness classes; arm B, receipt of free childcare combined with free weekly fitness classes; and arm C, receipt of free childcare combined with free weekly fitness classes and peer support activities. Over 2 years, we will recruit a pilot wave followed by 7 additional waves, totaling 720 participants into 24 fitness classes. Physical activity is the primary outcome, measured using accelerometers, but secondary outcomes also include physical activity assessed using a self-reported questionnaire and attendance data. We will assess additional secondary outcomes (eg, health status, depression, and anxiety) and mediators or moderators (eg, social support and cohesion) with a baseline and follow-up questionnaire. The intention-to-treat analysis will use linear mixed-effects models to assess the main intervention effects on physical activity outcomes and other secondary outcomes. Ethnographic methods will examine how intersecting forms of social identity shape women’s experiences of physical activity and understand how real-world conditions shape the intervention implementation.

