###### Attendance

An additional process outcome will be attendance at fitness classes. Participation rates are arguably the most important process outcome of interest when evaluating the success of an intervention like FT4W. Shape Up NYC takes attendance at each fitness class, and community champions will take attendance for the peer support activities to understand participation, retention, and attrition levels.

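### Social cohesion and MVPA are measured in the same follow-up window, so the two stated mediation models cannot show which one drives the other, and the causal label should be dropped for cohesion

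*Protocol article*

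**What the plan says.** The Quantitative Analysis section names two kinds of mediator, environmental resources and social cohesion: "We will conduct mediation analysis to test whether environmental resources and social cohesion, described under working mechanisms, mediate the intervention effects". It then fixes both models: "The first model will use the outcome measure as a dependent variable and treatment arm and mediator as predictors" and "The second model will use the mediator as a dependent variable and treatment arm as the predictor". Each has a cluster-specific random intercept. The result carries a causal label: "Causal mediation effects will be tested using the R package" called mediation.

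The Abstract describes "mediators or moderators (eg, social support and cohesion) with a baseline and follow-up questionnaire", so there is one measurement after baseline. The Social Cohesion and Support section adds that the Sense of Community Index-2 is given at follow-up only. The Follow-Up Assessment section says: "At week 10, study staff will again mail Axivity AX3 watches to participants and links to complete the online follow-up questionnaire". It adds that the baseline procedure is repeated and that participants count as lost only if nothing has arrived by week 16. Table 2 ticks the follow-up accelerometer and the follow-up questionnaire in the same columns, W10 to W12.

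On attendance, "Shape Up NYC takes attendance at each fitness class", and Table 2 ticks attendance collection in every column from W1 to W12. The mediation paragraph does not mention attendance.

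**The concern.** A mediation claim needs the mediator to act before the outcome, and randomising the arm does not randomise the mediator. Here the only post-baseline cohesion score comes from the same window as the MVPA it is meant to explain, after about ten weeks of group classes. Mothers who attend and move more also meet more people, so activity may raise cohesion. The protocol links the two itself: under Fidelity, the ethnographer observes interaction around the class as an indicator of cohesion. The two models would read an association in either direction as mediation.

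What is at stake is the mechanism conclusion, in particular whether peer support works through cohesion. The trial also logs class attendance, which does have a time order and is the most direct route by which childcare at the class could act. The mediation plan leaves it out.

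**Working it through.** **Timing, set side by side**

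| Item | When | Where stated |
|---|---|---|
| Cohesion and social support scores | Baseline and follow-up only | Abstract, Methods |
| Sense of Community Index-2 | Follow-up only | Social Cohesion and Support |
| Follow-up watch and questionnaire link | Both sent at week 10; both ticked W10-W12 | Follow-Up Assessment; Table 2 |
| Latest response | Week 16 | Follow-Up Assessment |
| Class attendance | W1-W12 | Attendance; Table 2 |

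Cohesion is not measured between baseline and week 10. Only attendance in weeks 1-9 clearly precedes the outcome window. A class attended in the wear week is itself part of the measured activity.

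The self-reported outcome is more exposed. The IPAQ recalls the past 7 days, so a cohesion score given at the same questionnaire sitting follows the recalled activity.

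**Size of the possible error**

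The plan gives no figure for the mediation analysis, so there is nothing to reproduce. Inputs from Sample Size: 7 sites per arm, 15 analysed participants per site, ICC 0.15, and d=0.75 (the stated minimum detectable effect for aim 2). Assumed, not in the documents: a within-arm correlation ρ between cohesion and MVPA of 0.2, 0.3 or 0.5, arising wholly from activity to cohesion.

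Model: MVPA is Y = δ·arm + class effect (variance 0.15) + error (variance 0.85). Cohesion is M = γY + noise (variance 1), with γ = ρ/√(1−ρ²). There is no path from M to Y.

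Hand calculation at δ = 0.75, ρ = 0.3:
- γ = 0.3/√0.91 = 0.3145.
- Arm to mediator: a = 0.75 × 0.3145 = 0.236.
- Variance of a class mean of M: 0.15γ² + (0.85γ² + 1)/15 = 0.0148 + 0.0723 = 0.0871.
- SE(a) = √(2 × 0.0871/7) = 0.158, so a/SE = 1.495.
- Chance that a is significant: P(Z > 1.96 − 1.495) = 0.32.
- Mediator to outcome, given arm: b ≈ 0.85γ/(0.85γ² + 1) = 0.2673/1.0841 = 0.247. This is about five standard errors from zero, so a governs the result.
- False share mediated: a·b/δ = γ·b = 0.3145 × 0.247 = 0.078.

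The same steps at ρ = 0.5 give a/SE = 0.433/0.197 = 2.20, a probability of 0.59 to 0.60, and a share of 0.22.

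Simulation of the two random-intercept models (REML, 21 clusters of 15, arm C versus A, 95% Monte Carlo interval for a·b, 800 runs per setting) gave:

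| True arm effect | ρ = 0.2 | ρ = 0.3 | ρ = 0.5 |
|---|---|---|---|
| 0 | 4% | 6% | 6% |
| 0.75 | 15% | 31% | 60% |
| 1.0 | 25% | 51% | 84% |
| 1.8 (effect cited in Sample Size) | 59% | 94% | 100% |

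The false share mediated is about 4%, 8% and 23% across the three correlations. A separate simulation of C versus B with 7+7 classes (600 runs per scenario) gave 32% and 60% at d=0.75 for 0.3 and 0.5, and 13% and 21% at d=0.40. With no arm effect the rate stays near 5%, so the excess comes from the reverse path and not from the test.

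**The case against.** **The order of the survey.** A reader might infer that the mediator is always taken together with, or after, the outcome. The documents do not support that. Follow-up is said to copy the baseline procedure, in which the watch is sent once the survey is complete, so some questionnaires could precede the wear days. Week 16 is a loss-to-follow-up limit, not a schedule. Against that, the same section sends the watch and the link together at week 10, so the order is not fixed. A survey answered a few days earlier still follows about ten weeks of classes.

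**Resources.** A reader might extend the point to the resource mediators. No reason appears in the documents why more MVPA would raise insurance cover, food security or childcare access, and arms B and C receive childcare by design. The reverse path is not shown there.

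**Attendance.** A reader might infer that attendance is treated only as a process measure, or that it should displace the planned mediators. The Abstract also lists it as a secondary outcome, so its comparison by arm is already covered by the mixed models. The planned mediators come from the stated theory, and ranking attendance above them would be a preference. Attendance is also not randomised: motivation and earlier activity can drive both attendance and MVPA.

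**Assumptions and the analysis plan.** The correlations are assumed and the forward path is set to zero, so the simulation shows what the models would do if the reverse path held, not that it holds. Covariates and sensitivity analyses for mediation may be in an unseen analysis plan, and their absence from the article is no fault. This stands. The point rests on what the article does fix: the models, the single follow-up measurement and the causal label.

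**Conclusion.** The concern holds for social cohesion. One post-baseline score, taken close to the MVPA week and after about ten weeks of intervention, cannot establish direction under the two stated models. If the association came wholly from activity to cohesion, with correlation 0.2 to 0.5 (assumed), about 15% to 60% of trials at d=0.75 would declare mediation that does not exist, against a nominal 5%. The false share mediated would be about 4% to 23%. The false-positive rate rises with the intervention effect, so the risk is greatest when the trial succeeds.

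The point limits what may be concluded about mechanism. A reader might infer that aims 1 and 2 are undermined. They are not: those aims are tested by arm contrasts on MVPA, which do not use the mediator.

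**What to change.** In the mediation paragraph of Quantitative Analysis:

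1. Report the cohesion mediation as associational and drop the causal label for it, giving the shared measurement window as the reason.
2. Include baseline MVPA in both models, and the baseline mediator where one exists (the Sense of Community Index-2 has none). This reduces confounding by stable differences between mothers; it does not settle direction.
3. Add the number of fitness classes attended in weeks 1-9 as a further, not primary, mediator for B versus A and C versus B, using the same pair of mixed models.
4. State that attendance supplies time order but is not randomised, so its mediation result also depends on no unmeasured confounding.

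The cost is one more mediation model and weaker wording of the mechanism claim. Attendance is already logged in all arms. Data collection is expected to run until September 2026, so the change can be specified before the final analysis.
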